**Fig. 3 Fig3:**
[figure not shown]
Timeline of the Healthy High School intervention

### Project name and visual identity

The study is registered as the HHS study in the trial registry. In Danish, the project is named *en go’ Bgym’* - a wordplay meaning ‘a good start in high school’. We chose a project name with a humorous tone to appeal to young people without focusing on health. The pictorial material is designed to express situations from everyday life that students can relate to. ‘Real’ students are used instead of professional models to represent different types of students. The project name and visual identity was developed in close collaboration with a professional graphic designer.

### Implementation

The implementation of the HHS intervention was initiated in the school year 2016/17. Prior to the start of the intervention, we asked principals at all intervention schools to recruit two school coordinators; one among students and one among school staff (e.g. a teacher or the head of training division). Their tasks were to receive and redistribute information about the HHS study from the research group to teachers and students and to work as local project ambassadors. Implementation was launched by a one-day kick-off conference in the beginning of the school year 2016/17. The school coordinators and up to three other school representatives (e.g. teachers, student counsellors, canteen staff and student councils) were invited to participate. The kick-off conference was opened by a famous Danish brain researcher giving a keynote speech on the adolescent brain in relation to the main themes of the intervention. Furthermore, the research group gave a comprehensive presentation of the main goals and rationale of the intervention, an introduction to the intervention components and an overview of the evaluation design of the study. The participants experienced some of the intervention components during the conference. They met the canteen consultant who was going to visit all high schools during the intervention  period  (mandatory environmental change  initiative). They were encouraged to discuss how to implement selected interventions components during four different workshops; one that focused on the Young & Active initiative, and three that focused on the stress and sleep related initiatives. Implementation manuals for all intervention components have been developed to accompany this complex intervention. The planning of implementation and sustainability will be described in detail in a separate paper ([name] et al., in preparation).

### Data collection

The following data was collected for the effect evaluation of the HHS study: 1) self-reported questionnaires from students and school administrators, 2) registration of students’ perceived stress by text messages, and 3) objective assessment of PA by accelerometer measures. All data were collected simultaneously at the intervention and control schools.

#### Student questionnaires

The student questionnaire is mainly based on validated measures from the DNYS [30] and the Health Behaviour in School-aged Children (HBSC) study [45] and supplemented with items from other studies including the Boost study [46] and the Pro Children study [47]. The items were either transferred directly or adjusted according to our study population. New items were developed specifically related to the HHS study. The questionnaire covers the following themes: socio-demographics, well-being, stress, sleep, sense of community, PA, eating and meal habits, social relations, school life, potential determinants of outcome measures, implementation measures, positive and negative side effects. The questionnaire was pre-tested among the research group and colleagues to assess time range for answering and phrasing of the questions, resulting in slight revision. New items that were related to implementation of the study and developed for the follow-up questionnaires were pilot tested on 10 students from one intervention school and revised according to observations and the students’ comments. Table 2 summarises the quantitative measures included in the HHS surveys.

**Table 2 Tab2:** Quantitative data collection of the Healthy High School study

Key measures	Operationalization	Instrument	Timing of collection^*^	Data source
PRIMARY OUTCOME				
Well-being	WHO-Five Well-Being Index, Cantril Ladder of Life Scale	Web-based questionnaire	Baseline, 1st follow-up and 2nd follow-up	Students
SECONDARY OUTCOMES				
Stress	10-item Perceived Stress Scale Stress intensity, stress frequency	Web-based questionnaire Web-based questionnaire;text-messages	Baseline, 1st follow-up and 2nd follow-up Baseline, 1st follow-up and 2nd follow-up; once a month from September 2016–June 2017	Students Students; subsample of students
Sleep	Sleep quantity, sleep quality	Web-based questionnaire	Baseline, 1st follow-up and 2nd follow-up	Students
PA	Hours of moderate-to-vigorous PA per week Average daily PA	Web-based questionnaire Accelerometer	Baseline, 1st follow-up and 2nd follow-up Baseline, 1st follow-up	Students Subsample of students
Sedentary behaviour	Hours of daily sedentary time	Web-based questionnaire; accelerometer	Baseline, 1st follow-up and 2nd follow-up; baseline, 1st follow-up	Students; subsample of students
Meal habits	Daily intake of breakfast, lunch and water	Web-based questionnaire	Baseline, 1st follow-up and 2nd follow-up	Students
Sense of community	High school sense of community School class sense of community	Web-based questionnaire Web-based questionnaire	Baseline, 1st follow-up and 2nd follow-up 1st follow-up and 2nd follow-up	Students Students
PROXIMAL OUTCOMES				
INDIVIDUAL DETERMINANTS^**^				
Knowledge	Knowledge of stress, national dietary guidelines, PA guidelines and sleep recommendations	Web-based questionnaire	1st follow-up	Students
Awareness	Awareness of whether they meet national dietary guidelines, PA guidelines and sleep recommendations, and of own stress symptoms	Web-based questionnaire	Baseline, 1st follow-up and 2nd follow-up	Students
Self-efficacy	General self-efficacy	Web-based questionnaire	Baseline, 1st follow-up and 2nd follow-up	Students
Outcome expectations	Perceived effects of PA, sleep, eating breakfast/lunch, e.g. more energy, stress relief, better sleep	Web-based questionnaire	Baseline, 1st follow-up	Students
Skills	Time management skills, stress management	Web-based questionnaire	Baseline, 1st follow-up	Students
Perceived barriers and facilitators	Barriers and motivation for PA and eating regular meals	Web-based questionnaire	Baseline, 1st follow-up	Students
Perfectionism	Concern over mistakes, personal standards	Web-based questionnaire	Baseline, 1st follow-up	Students
INTERPERSONAL DETERMINANTS				
Peer- and school staff influence	Social norms, social support	Web-based questionnaire	Baseline, 1st follow-up and 2nd follow-up	Students, school administrators
ORGANISATIONAL DETERMINANTS				
Environmental conditions at school and local community	Physical, economical, political and structural	Web-based questionnaire	Baseline, 1st follow-up and 2nd follow-up	School administrators
POTENTIAL POSITIVE SIDE EFFECTS				
Healthy weight development	Body mass index determined from weight and height	Web-based questionnaire	Baseline, 1st follow-up and 2nd follow-up	Students
Energy for academic achievement	Maintenance of energy during the school day	Web-based questionnaire	Baseline, 1st follow-up	Students
Maintain concentration throughout the school day	Morning and afternoon concentration	Web-based questionnaire	Baseline, 1st follow-up	Students
Decrease in school absence	The number of school days missed due to absence the past 30 days	Web-based questionnaire	2nd follow-up	Students
Decrease in intake of unhealthy food & drinks	Intake of soft drinks, energy drinks and unhealthy snacks	Web-based questionnaire	Baseline, 1st follow-up and 2nd follow-up	Students
POTENTIAL UNINTENDED ADVERSE EFFECTS				
Negative body image	Negative body perception, body weight dissatisfaction	Web-based questionnaire	Baseline, 1st follow-up and 2nd follow-up	Students
Sports injuries	Sport injuries the past 6 months	Web-based questionnaire	Baseline, 1st follow-up and 2nd follow-up	Students
Dieting	Dieting the past 6 months	Web-based questionnaire	Baseline, 1st follow-up and 2nd follow-up	Students
MODERATORS				
Gender	Boy/girl	Web-based questionnaire	Baseline, 1st follow-up and 2nd follow-up	Students
Socioeconomic position	Family occupational class, parental education	Web-based questionnaire	Baseline, 1st follow-up and 2nd follow-up	Students
IMPLEMENTATION				
Implementation measures	Dose (delivered and received), fidelity, appreciation, acceptability, context	Web-based questionnaire	1st follow-up	Students, teachers, school administrators

PA = physical activity. ^*^Baseline (August 2016), 1st follow-up (May 2017), 2nd follow-up (April 2018). ^**^ Determinants are measured for all primary and secondary outcomes. These determinants will be described in detail in future articles

A week before data collection, information materials were sent to school coordinators with separate material to each school class including unique passwords for each of the students to access an internet-based questionnaire. Students answered the questionnaire in class after a standardised instruction given by a teacher. The questionnaires can be completed within one school lesson of 45 min. Teachers were asked to encourage absent students to answer the questionnaire at a later timer. E-mails were sent to the school coordinator with an enquiry of reminding school classes of the data collections where no or few students completed the questionnaire within the timeframe.

#### School administrator questionnaires

The items for the school administrator questionnaire were developed specifically for the HHS study by the research group. The items are inspired by staff questionnaires from the DNYS [30], the HBSC study [45], the Boost study [46] and the X:IT study [48]. The questionnaire covers the following themes: Structural, physical, educational and social school environment with a specific focus on past and ongoing initiatives regarding well-being, sense of community, stress, sleep, PA and meal habits as well as organisational capacity to implement health promoting initiatives. The 20-min questionnaire was completed by the principal or school coordinator.

#### Student registration of perceived stress

Students accepted to participate in a monthly sub-study about perceived stress where text messages were used for data collection by typing their telephone number in the baseline questionnaire. The aim of this sub-study is to explore how students’ levels of stress fluctuate throughout a school year. Students received a text message the last Wednesday of each month (from September 2016 to June 2017) with the following question: 1) *Do you feel stressed? Write* e.g. *0 if your answer is ‘No, not at all’. Write only one number (0. No, not at all, 1. Yes a little, 2. Yes, a lot)*. After replying to the first message a second message was sent: 2) *How often have you felt stressed during the last month? Write* e.g. *1 if your answer is ‘A few days’. Write only one number (0. Never, 1. A few days, 2. Weekly, 3. Daily)*. If the students did not answer the questions within 24 hours, a reminder was sent automatically. An outro message was sent to all students after each data collection including contact information to a free telephone and online counselling service specifically for young people. A prior the data collection, a small pilot study was conducted to test phrasing of the text messages, guidance for answering the questions and whether the technique was working.

#### Objective assessment of PA

PA was objectively measured using Axivity AX3 accelerometers in a sub sample of two intervention schools and two control schools at baseline and first follow-up. Axivity AX3 accelerometer was attached directly to the skin of the front thigh of participating students by trained research staff. For up to seven consecutive days, the participants were instructed to wear the accelerometers all the time (including water activities and sleep). Acti 4 software will be used to discriminate between PA types including sitting, standing, walking, fast walking, running, cycling, sit-to-stand movements (i.e. transitions from sitting to upright stand), and number of steps based on threshold values of standard deviation of acceleration and the derived inclination [49].

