### Specific objectives

The primary objective is to assess the effectiveness of the HHS intervention by comparing subjective well-being in intervention and control schools. Study hypothesis: at 9-month follow-up there will be a 6%-point difference in the prevalence of students with a high level of life-satisfaction in intervention schools compared to control schools. This difference will be sustained at 20-month follow-up.

Secondary objectives are to compare differences in the following outcomes between the two groups at 9-month and 20-month of follow-up: Perceived stress, sleep quantity and quality, PA, meal habits, and sense of community within the school class and at school. Additional objectives are to conduct a mixed-methods process evaluation and a health economic evaluation.

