### Secondary outcome measures, proximal outcomes and side effects

*Secondary outcomes* are measured at all three time points in the student questionnaire and include: 1) stress measured by the 10-item Perceived Stress Scale as well as stress intensity and stress frequency, 2) sleep measured by sleep quantity and quality, 3) PA measured by hours of moderate-to-vigorous PA per week, hours of daily sedentary time and average daily PA, 4) meal habits measured by daily intake of breakfast, daily intake of lunch, daily intake of snacks and daily intake of water, and 5) sense of community within the school class and at school.

*Potential positive side effects* (such as healthy weight development, high perceived levels of energy for academic achievement, high perceived ability to concentrate during school day, decrease in school absence, decrease in intake of unhealthy food and drinks) and *unintended adverse effects* (such as negative body image, sports injuries and dieting) are measured in the student questionnaire at all three time points. *Proximal outcomes* include individual determinants (measured in the student questionnaires), interpersonal determinants (measured in the student questionnaires and in the school administrator questionnaires), and organisational determinants (measured in the school administrator questionnaires) (Table 2).

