### Planned statistical analyses

The presentation of study findings will be in accordance with CONSORT guidelines for cluster-randomised controlled trials [58]. We will apply multilevel methods to analyse the effect of the intervention on the primary and secondary outcomes taking the hierarchical nature of data (students nested within classes nested within high schools) into account. We will apply an intention-to-treat approach and use multiple imputations to impute missing data as suggested by Graham (2012) [59]. To improve precision, estimates will be adjusted for baseline measurements of prognostic variables [60]. All further impacts of the intervention such as intended proximal effects (determinants), potential positive side effects and unintended adverse effects will also be subject to evaluation. We will analyse effectiveness of the intervention in different socio-demographic subgroups such as boys and girls and high and low socio-economic position. Based on the multiple pathway approach, mediation analyses will be used to examine whether changes in primary outcomes are following changes in secondary outcomes and determinants [61, 62]. The mediation analyses will be completed by Stata Software (StataCorp LP, College Station, Texas).

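### Accelerometer average daily PA and sedentary time are secondary effect outcomes measured in only two schools per arm, too few for the planned multilevel comparison to be both valid and informative

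*Protocol article*

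**What the plan says.** - **Role.** The Data collection section names "objective assessment of PA by accelerometer measures" as the third data source for the effect evaluation. The secondary outcomes section ends its PA item with "hours of daily sedentary time and average daily PA".
- **Source.** In the PA row of Table 2 (Student questionnaires section) the measures are "Hours of moderate-to-vigorous PA per week Average daily PA" and the instruments, in the same order, are "Web-based questionnaire Accelerometer". Read in that order, MVPA comes from the questionnaire in all students at three time points. Average daily PA comes only from the accelerometer, in a subsample, at baseline and 1st follow-up. Daily sedentary time has both sources.
- **Number of schools.** The section on objective assessment of PA says that the accelerometers were used "in a sub sample of two intervention schools and two control schools at baseline and first follow-up".
- **Analysis.** Planned statistical analyses states: "We will apply multilevel methods to analyse the effect of the intervention on the primary and secondary outcomes". The levels are students, classes and schools. No separate rule is given for the accelerometer subsample.
- **Time points.** Specific objectives says: "Secondary objectives are to compare differences in the following outcomes between the two groups at 9-month and 20-month of follow-up", and PA is on that list. The secondary outcomes section says that these outcomes "are measured at all three time points in the student questionnaire and include" the listed measures, one of which is average daily PA.

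**The concern.** Schools were randomised, so the evidence on an arm difference comes from variation between schools. With two schools per arm that variation is estimated on 2 degrees of freedom. A multilevel model with large-sample inference treats the estimate as if it were well determined and rejects too often. A method that allows for the uncertainty gives a very wide interval. In both cases an objective PA effect, reported beside secondary outcomes from 30 schools, could be given weight that it does not carry. The article counts the objective measures among its strengths, and its abstract mentions only a subsample of students, so a reader of the abstract would not learn that there are four schools.

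There is also a conflict in the text. A measure that Table 2 ties to the accelerometer and to two time points is described elsewhere as a questionnaire item at three, and PA is promised at 20 months.

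**Working it through.** **1. The plan's own figure.** For 22% against 28%, two-sided 5%, 80% power and continuity correction, 850 students per arm are needed. The design effect is 1 + (221 − 1) × 0.01 = 3.2. Then 850 × 3.2 / 221 = 12.31, rounded up to 13 schools per arm, or 26 in total. This reproduces the stated figure. It concerns the Cantril Ladder only; the article gives no calculation for accelerometer outcomes.

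**2. Inputs for the accelerometer comparison.**
- Schools per arm: k = 2 (objective assessment of PA section).
- Students per school (m) and ICC (ρ): not given for accelerometry. Assumed m = 50 to 221 and ρ = 0.01 to 0.10. The low end of ρ and the high end of m are the article's Cantril Ladder values.
- Outcome SD set to 1. The class level and baseline adjustment are left out.

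**3. Degrees of freedom.** 2k − 2 = 2, so the two-sided 5% critical value is 4.30. With 15 schools per arm there are 28 df and the value is 2.05. The normal value is 1.96.

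**4. Type I error of a nominal 5% test.** Simulation of a balanced random-intercept model under the null, with 1,000,000 runs per setting for two schools per arm:

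| ρ | m | REML, z | ML, z | School-mean t, 2 df |
|---|---|---|---|---|
| 0.01 | 50 | 7.1% | 9.6% | 5.0% |
| 0.01 | 221 | 13.1% | 19.2% | 5.0% |
| 0.02 | 100 | 12.7% | 18.6% | 5.0% |
| 0.05 | 100 | 16.2% | 24.9% | 5.0% |
| 0.10 | 221 | 18.5% | 29.2% | 5.0% |

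REML with a 2-df t reference is conservative (0.0% to 4.3%). With 15 schools per arm the z-tests reject in about 6% (REML) and 7% (ML).

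**5. Precision of the valid test.** The variance of the arm difference is (2/k) × [ρ + (1 − ρ)/m], which for k = 2 is ρ + (1 − ρ)/m. The 95% half-width, taken at the true standard error, is 4.30 × √[ρ + (1 − ρ)/m]:
- ρ = 0.02, m = 100: 4.30 × √0.0298 = 0.74 SD
- ρ = 0.05, m = 100: 4.30 × √0.0595 = 1.05 SD
- ρ = 0.10, m = 100: 4.30 × √0.109 = 1.42 SD
- extremes of the grid: 0.52 SD (ρ = 0.01, m = 221) and 1.48 SD (ρ = 0.10, m = 50)

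The difference detectable with 80% power is 0.68 to 1.94 SD, against 0.13 to 0.36 SD with 15 schools per arm. Power for a 0.2 SD difference is 7% to 17%, against 34% to 99%. A permutation test has 4!/(2! 2!) = 6 allocations, so its smallest two-sided p-value is 2/6 = 0.33.

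**6. Instrument and timing of average daily PA, side by side.**

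| Place | Instrument | Time points |
|---|---|---|
| Table 2 | Accelerometer, subsample | Baseline, 1st follow-up |
| Objective assessment of PA | Accelerometer, four schools | Baseline, 1st follow-up |
| Secondary outcome measures | Student questionnaire | All three |
| Specific objectives (PA in general) | Not stated | 9 and 20 months |

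The first two rows agree. The third conflicts with them on both columns. The fourth cannot be met by this measure.

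**The case against.** The strongest reply is that the article commits only to multilevel methods. It names no estimator, Wald test or degrees-of-freedom rule, and such detail belongs in an analysis plan that is not shown. This stands in part: the inflated error rates describe what happens under normal-theory inference, not what the article says will be done. But an analysis plan can choose the inference and cannot add schools, so the choice is between an anti-conservative test and one with almost no power.

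Second, the accelerometry is called a sub-study, has a feasibility purpose as well, and is marked in Table 2 as a subsample at two time points. The success indicator concerns life satisfaction alone. All of this is so, but none of it takes the measures out of the secondary outcomes or the effect evaluation.

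Third, baseline adjustment could narrow the interval. It could, by an amount that the document does not allow one to estimate. It adds no schools.

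Several stronger readings are tempting and are not supported:
- That any p-value from four schools is invalid. A 2-df t-test on school means keeps 5% if those means are roughly normal.
- That a false positive is likely. Its probability is raised, to at most about 29% over the range examined.
- That a null result says nothing. It would still exclude very large differences.
- That sedentary time is known in only four schools. It is also self-reported by students in all schools, as is MVPA; only average daily PA depends wholly on the subsample.
- That these are confirmatory outcomes. The article does not use that term for them.

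**Conclusion.** The point holds as a cheap improvement. Average daily PA and accelerometer sedentary time sit among the secondary effect outcomes and fall under the planned multilevel analysis, yet rest on two schools per arm. Over the assumed ICCs and school sizes, normal-theory multilevel tests would reject a true null in about 7–19% (REML) or 9–29% (ML) of trials instead of 5%. A valid 2-df analysis would leave an interval of about ±0.7 to ±1.4 SD for 100 students per school and ICCs of 0.02 to 0.10, or ±0.5 to ±1.5 SD over the whole range. The sizes depend on those assumptions; the 2 degrees of freedom, the missing 20-month measurement and the conflict with Table 2 do not. The primary outcome and the self-reported PA outcomes are unaffected.

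**What to change.** 1. In the secondary outcomes section and Table 2, label average daily PA and accelerometer sedentary time as exploratory or descriptive sub-study outcomes, reported school by school.
2. If a between-arm estimate is given, base it on small-sample (2-df) inference, show its interval, and state that it rests on four schools.
3. Keep self-reported MVPA and sedentary time, from all 30 schools, as the PA outcomes for effectiveness at 9 and 20 months.
4. Reconcile the secondary outcomes section with Table 2 on instrument and time points, and say in Specific objectives that accelerometer measures do not extend to 20 months.

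No new data are needed. The cost is rewording and giving up a claim of an objectively measured PA effect, which four schools could not have supported.
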